## Abstract

**Background:**

Deaf persons are considered a high-risk population for health disparities.
During the covid-19 epidemic, deaf persons also suffer from psychological
issues, post-traumatic stress disorder, and seropositive HIV.

**Objective:**

This study aims to examine the effectiveness of an mobile health educational
program to increase mental health and HIV prevention among deaf
community

**Methods:**

This study employs a quasi-experimental design with a non-randomized
controlled trial, involving single-blinded participants and a parallel group
assignment, purpose for health service research, study phase 2-3. pronounced
to escalate the sample size to 40 deaf per group, which is 80 total
participants.

**Results:**

The analysis of the data will be conducted utilizing the generalized
estimation equation, with a confidence interval set at 95%. Significant
differences, both between and within groups, will be identified at a
threshold of P<.05. The findings of this study highlight the efficacy of
a mobile educational program in enhancing mental health and preventing HIV
within the deaf community. Furthermore, the outcomes of this research will
augment existing knowledge regarding psychological distress, HIV prevention
practices, and coping self-efficacy among individuals who are deaf.

**Conclusion:**

The intervention group is expected to demonstrate significantly lower scores
in psychological distress during both the immediate evaluation and the
assessment conducted three months post-intervention, compared to the
wait-list group. Additionally, the intervention group is anticipated to
exhibit enhanced levels of HIV prevention practices and coping
self-efficacy, resulting in a greater degree of adjustment.

**Clinical trial:**

SLCTR/2024/039, 25 November 2024, https://slctr.lk/trials/slctr-2024-039

## Introduction

HIV prevention in the deaf-disabled population is one of the HIV-related health
program’s concerns ( United Nations, 2016; World Health Organization (WHO), 2021b). Health initiatives relating to the promotion and prevention of
sexual and reproductive health, particularly HIV illness, are often more accessible
to those without disabilities. This is due to the fact that persons with impairments
are seen as sexually inactive and thus get less attention from HIV initiatives (
Schenk et al., 2020). At the
institutional level, the lack of knowledge and capacity of health workers on sexual
and reproductive health issues, the negative attitude and lack of sensitivity of
health workers, and the absence of privacy and accessible infrastructure for persons
with disabilities are barriers that many people with disabilities encounter when
attempting to access these services ( Schenk et al., 2020).

Persons with disabilities are 1.1 to 2.05 times more likely to engage in HIV-risk
behaviors, such as substance misuse, alcoholism, sexual activity without the use of
a condom, and partner switching. Awareness of HIV testing is also 1.1 times lower
among people with disabilities compared to the general population ( Doyle et al., 2021). Interestingly, earlier
research supporting the feasibility study indicate that only 28.9% of deaf persons
had undergone an HIV screening examination ( Olakunde & Pharr, 2020).

In addition to the absence of HIV-related information for the deaf, psychological
issues are also a common obstacle. Hearing loss at any age is also associated with
anxiety, low self-esteem and worth, cognitive decline, and diminished health-related
quality of life as well as psychological distress ( Mehboob Khan et al., 2019). Adults and teenagers alike are at
risk for very negative outcomes when they are experiencing psychological distress.
The effect is a breakdown in social and psychological functioning ( Alika et al., 2016; Fergusson & Woodward, 2002).

Deaf persons was linked to distress in a major sample of persons under 70 years of
age ( Bosdriesz et al., 2017; National Insitute on Aging (NIA), 2018).
During the COVID-19 epidemic, deaf persons also suffer from psychological issues and
post-traumatic stress disorder. The incidence of PTSD and depression among Hearing
loss and hearing teens before to and during the COVID-19 epidemic in four Iranian
cities (Borujerd, Malayer, Nahavand, ands Tuyskán). In our research, the
prevalence of PTSD (46.43%) and depression (41.07%) among teenagers with hearing
loss was much greater than predicted ( Ariapooran et al., 2021).

Their failure to establish good verbal communication may result in social rejection,
a lack of education, and a poor work position, all of which have a significant
negative influence on their self-esteem ( Gotowiec et al., 2022; Munoz-Baell & Ruiz, 2000; Strong & Shaver, 1991). The study of Jambor and Elliott (2005) on the self-esteem and coping methods of deaf students and deaf
children indicated that deaf persons who identify with the deaf culture acquired
higher self-esteem than those who identified with the hearing culture and involving
physical appearance in hearing impaired (  Indiana et al., 2021; Jambor & Elliott, 2005; Theunissen et al., 2014).

According to WHO estimates, Over 5% of the world’s population, or 430 million
individuals, have ‘disabling’ hearing loss and need rehabilitation
(432 million adults and 34 million children). It is anticipated that by 2050,
approximately 700 million individuals, or one in ten, would suffer from hearing
impairment. Less than one percent of deaf, hard of hearing, and deaf and blind
children in underdeveloped nations have access to school ( World Health Organization (WHO), 2021a). According to World
Federation of the Deaf (WFD) data, 80% of deaf persons are illiterate or poorly
educated ( El-Soud & Hassan, 2009).
Deaf persons have difficulty understanding health recommendations ( Bahareh & Heidary, 2015). Due to their
communication difficulties, limited understanding of deaf persons makes their health
treatment more hard ( Harmer, 1999).
According to research conducted by the England Mental Health Institute, there is a
clear correlation between psychological diseases and hearing loss; the incidence of
psychological issues among deaf children is almost double that of hearing children
(40% against 25%). According to research conducted in several nations, psychiatric
illnesses are manifestly more widespread among deaf persons ( National Health Service, 2005). Even in the United States,
less than 5% of deaf individuals get mental health treatment, and in the majority of
impoverished nations, there is no mental health care for the deaf ( Joseph AM, 2009).

There are challenges for the deaf person to get health information ( Folkins et al., 2005). Deaf persons and their
families need information and education to enhance general understanding of their
condition. One of the educational components for deaf and hard of hearing
individuals is the use of educational technology, such as computers and distant
learning ( Kelly & McKenzie, 2018).
Multimedia distant information and communication services may serve as the standard
electronic platform for continuing deaf education ( Drigas et al., 2009). The hearing health sector as a dynamic
network shaped by innovation and regulation, ensuring quality and risk mitigation.
Innovation included both technological and non-technological advancements benefiting
consumers. Ethical alignment required consumer involvement in both processes to
address stigma and reduce health disparities. ( Boisvert et al., 2024).

Increasingly prevalent digital health technologies are employed for the prevention,
diagnosis, and treatment of mental health issues. There is minimal research on
mental health and HIV prevention in online initiatives for the deaf community.
Engagement involves individual users’ ideas and emotions, level of activity,
and opinions about technical features of the software, including characteristics of
usability and attractiveness ( O’Brien & Toms, 2013). User engagement is also intimately tied to a
program’s usability O’Brien & Toms (2013), which includes efficacy, efficiency, and user happiness (
The National Standards Authority of Ireland (NSAI), 2018).

Recent studies have begun to explore innovative approve to address these gaps. For
instance, a 2023 study highlighted the effectiveness of digital health interventions
in improving health literacy and self-efficacy among deaf individuals, demonstrating
a positive impact on their overall well-being ( Arias López et al., 2023). Educational interventions involving
sign language interpretation and involvement of personnel involved in hearing loss
resulted in significant increases in knowledge(Choi et al., 2023) The need cultural
sensitive health communication strategies tailored to the deaf community to enhance
engagement and understanding of health information in mental health ( Ulutorti, 2024).

Despite the proliferation of mobile health interventions in other populations, deaf
persons remain underserved due to linguistic and cultural barriers. This study seeks
to address that gap by evaluating a sign language-based mobile health program
tailored to this community.

**Clinical trial: SLCTR/2024/039, 25 November 2024**, https://slctr.lk/trials/slctr-2024-039.

## Methods

This quasi-experimental study follows a non-randomized controlled trial design, in
which participants are assigned to either the intervention group, receiving the
mobile health KaPi program, and the control group, receiving standard educational
materials in the form of e-books. To minimize potential bias, participants will be
blinded to their group allocation; they will not be informed whether they are
receiving the intervention or serving as part of the control group. Efforts will be
made to ensure that the delivery of content appears comparable across groups to
prevent participants from discerning their allocation. Data collection took three
months from the first intervention given. To ensure that the intervention carried
out is in accordance with the standards, the researcher using the Standard Protocol
Items as a guide. The study will adhere to the Standard Protocol Items:
Recommendations for Interventional Trials (SPIRIT) guidelines ( Chan et al., 2016), the Consolidated Standards
of Reporting Trials (CONSORT) criteria ( Schulz et al., 2010), and the recommendations set forth by the Consolidated
Standards of Reporting Trials of Electronic and Mobile Health Applications and
Online Telehealth (CONSORT-EHEALTH) ( Eysenbach et al., 2011). Participation in the study was voluntary, and no financial
compensation was offered. To ensure the accuracy and validity of this study, we will
take strategic steps to minimize bias. The study will start with clear, testable
objectives and hypotheses, and random sampling will be used to ensure
representativeness. Data will be collected using valid, reliable instruments and
standardized procedures. A blind or double-blind design will be implemented to
reduce bias from both researchers and participants. Data analysis will follow
appropriate statistical methods to avoid misinterpretation. The research process
will be transparently reported, with methods and results available for replication.
Peer review and potential replication by other researchers will further confirm the
findings, ensuring the study produces valid, unbiased results.

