### Study design

This study will employ a quasi-experimental, non-randomized controlled trial
design with single blinding applied to participants. The control group will
receive standard therapy, while the intervention group will receive the mobile
health program. A parallel assignment approach will be used, reflecting the
structure of health services research. This study corresponds to a Phase
2–3 trial, aiming to evaluate both the feasibility and preliminary
effectiveness of the intervention. One or two (experimental group) receives the
Mobile health KaPi Program intervention under test and the other (comparison
group or control) receives the standard e book/leaflet. Then follow up on the
two or more groups to see if there are any differences in the results. The
results of the study and subsequent analysis are used to assess the
effectiveness of the intervention mobile health application. Quasi-experimental
are the most rigorous way to determine if there is a causal link between
interventions and outcomes ( Polit and Beck, 2017).  Figure 1 provides an
overview of the study design. The choice of this experimental design is grounded
in its robustness and efficacy ( Creswell, 2016).

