### Recruitment

To assess eligibility, the researcher will initiate contact with all regional
leaders of Gerkatin NGOs within the target district, facilitated through
coordination with the head of Gerkatin in the Yogyakarta area. This process will
be accompanied by a formal data collection permit issued by the
researcher’s affiliated university. The letter will be forwarded to the
regional Gerkatin head, who will then distribute it to local branch leaders to
support coordinated recruitment.

The recruitment strategy will apply multiple approaches commonly used to enhance
participation in research, such as early notification to Gerkatin leadership,
offering involvement opportunities, on-site visits to Gerkatin representatives,
outreach via phone and digital communication, and allowing potential
participants to consult with research staff regarding study participation.
Dedicated research personnel will supervise and document the recruitment
process.

Once permission is obtained, the Gerkatin head or a designated representative
will contact eligible individuals via telephone to assess inclusion criteria and
confirm their willingness to participate. Eligible participants will be provided
with detailed information and consent forms, including explanations in
Indonesian Sign Language, and asked to sign written consent forms.

To support participant retention throughout the three-month study period, a
dedicated WhatsApp group (WAG) will be created for enrolled participants. This
group will serve as a monitored communication platform for sending reminders,
providing support, and addressing questions related to the intervention and
follow-up activities. Periodic check-ins and app-based notifications will also
be used to promote sustained engagement. Participants will be reminded of their
right to withdraw from the study at any time without penalty. All study
procedures and timelines will be clearly explained in the Respondent Information
and Consent Forms.

To address potential technological barriers, the study will ensure that all
participants have access to a smartphone compatible with the KaPi mobile
application. For participants without a suitable device, the research team will
collaborate with local Gerkatin branches to provide access to shared devices or
temporary loaner phones during the study period. In addition, brief orientation
sessions will be conducted in Indonesian Sign Language to improve digital

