**Mobile Health KaPi Program**

The KaPi mobile health program consists of 11 structured sessions, each lasting
approximately 12 minutes. These sessions cover topics such as HIV prevention
strategies, coping mechanisms for psychological distress, and self-efficacy
improvement, all delivered through Indonesian sign language videos within the
app. The program application can download at playstore with link https://play.google.com/store/apps/details?id=com.project.kapi.
for the table this program can acces at https://doi.org/10.5281/zenodo.14784226 ( [name], 2025b), Data are available under the terms of the
Creative
Commons Zero “No rights reserved” data waiver (CC0
1.0 Public domain dedication).

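### The blinding statements contradict each other, and participant blinding to allocation is not credible as described when one arm gets a sign-language video app and the other a PDF e-book or leaflet

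*Protocol article*

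**What the plan says.** The protocol article describes blinding in three places.

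- **Abstract, Methods paragraph, and Study design:** single blinding, of participants. Study design describes a quasi-experimental, non-randomised "design with single blinding applied to participants. The control group will" receive standard therapy.
- **Methods, opening part:** participants will be "blinded to their group allocation; they will not be informed whether they are" in the intervention or the control arm. Efforts will be "made to ensure that the delivery of content appears comparable across groups to" stop them from working out their arm.
- **Methods, later in the same paragraph:** "A blind or double-blind design will be implemented to" reduce bias from researchers as well as participants.

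The treatments are described elsewhere. The KaPi program has 11 sessions of about 12 minutes, "all delivered through Indonesian sign language videos within the" app (Mobile Health KaPi Program). The control arm receives an e-book or leaflet (Methods; Study design), and the e-book is a PDF (Ebook Mental Health and HIV/AIDS). The Abstract's conclusion calls the comparator a wait-list group.

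The primary outcomes are K10, the VCT knowledge, attitude and practice questionnaire, and CSE (Statistical analysis). That section expands CSE as communication self-efficacy, whereas the questionnaire section describes coping self-efficacy. I take them to be the same instrument.

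**The concern.** Two things are wrong as written. First, participant-only blinding and double blinding are different designs, and the article claims both. It describes no procedure for blinding any researcher or assessor. Second, the claim that participants do not know their allocation does not fit the treatments described.

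This matters because Methods offers blinding as a safeguard against bias, in a trial that has no randomisation to rely on. Most of the primary outcome data are the participants' own ratings. A reader who is told that the trial is participant-blinded, or double-blind, will discount expectation and response bias. The described design does not support that discount.

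**Working it through.** **Step 1. The blinding statements side by side.** The Abstract and Study design blind participants only. Methods first says participants are blinded, then promises a blind or double-blind design covering researchers and participants. A trial cannot be both single-blind for participants only and double-blind. This step needs no inference.

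**Step 2. Whether participant blinding is credible.**

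- *Format.* One arm opens an app and watches signed videos; the other opens a written PDF or leaflet. The language, medium and structure all differ.
- *Mitigation.* Methods states an aim of comparable appearance but names no measure.
- *Information given.* Study "procedures and timelines will be clearly explained in the Respondent Information" and Consent Forms (Recruitment), and the ethics section promises detailed information in sign language with comprehension questions. The forms are not shown, so what they say about the other arm is unknown.
- *Contact.* Participants are drawn from one NGO (Study area), and a WhatsApp group for enrolled participants is planned without a stated split by arm (Recruitment).
- *Comparator label.* If the control arm is a wait-list, as the Abstract says, its members would know they are waiting.

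**Step 3. Which outcomes are exposed** (Questionnaire section).

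| Outcome | How obtained | Exposure |
|---|---|---|
| K10 | Symptom questionnaire | Exposed |
| Coping self-efficacy | Self-rated confidence, 11-point scale | Exposed |
| VCT attitude | 5-item scale | Exposed |
| VCT practice | One question on previous use | Exposed |
| VCT knowledge | Scored by correct answers | Less exposed |

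**Step 4. An illustration of size.** The documents give no figure for bias, so every shift below is an assumption. The calculation uses the repeated-measures ANOVA from the Sample size section. It is not the planned GEE.

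Inputs from the article: N = 66, 2 groups, alpha 0.05, f = 0.20, and m = 3 measurement points (Statistical analysis). Assumed: correlation rho = 0.5 and sphericity.

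Formula: lambda = N·m·f²/(1 − rho), with df1 = m − 1 = 2 and df2 = (N − 2)(m − 1) = 128.

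*The plan's own figure:* lambda = 66 × 3 × 0.04/0.5 = 15.84, which gives power 0.950. The stated 66 reproduces.

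*Pure reporting shift:* assume no true effect and a between-arm shift of (0, b, b) SD at the three visits. The interaction effect size is then f = b/√18, so at rho = 0.5 lambda = 66 × 3 × b²/(18 × 0.5) = 22b².

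| Shift b (SD) | f | lambda | Chance of P<.05 |
|---|---|---|---|
| 0.1 | 0.024 | 0.22 | 6.7% |
| 0.2 | 0.047 | 0.88 | 12.0% |
| 0.3 | 0.071 | 1.98 | 21.9% |

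The result depends on the assumed correlation. At b = 0.3, rho = 0.3 gives lambda 1.41 and 16.7%; rho = 0.7 gives lambda 3.30 and 34.3%.

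**The case against.** The best defence is that Methods explains the blind as not telling participants whether they are in the intervention or the control arm. Both arms receive digital education on mental health, coping and HIV. Someone reading the e-book knows its format but need not know that it is the comparator. This stands in part, so the claim that the blind could not possibly hold goes too far. But being unaware of which arm is under test is not the same as being blinded to allocation, and it is allocation blinding that the article claims.

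A reader might also infer more than the documents support:

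- *That controls will certainly know their arm because the trial is presented to them as an app trial.* The title page and consent forms are not shown, so this cannot be established.
- *That notifications and app orientation mark out the app arm.* Recruitment describes these for the study as a whole, without a split by arm.
- *That expectation bias is the leading alternative explanation.* Allocation is not random, and baseline confounding is at least an equal rival.
- *That the VCT knowledge items should now carry the conclusion.* They are less exposed, but re-ranking the declared primary outcomes is a preference and does not follow from this point.

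Finally, the numerical illustration shows what a given shift would do. It does not show that such a shift exists.

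**Conclusion.** The point holds. The blinding statements contradict each other, and blinding of participants to allocation is not credible as described. The first part rests on the text alone. The second rests on the described formats and on the absence of any named masking measure.

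The consequence is limited but real. For K10, coping self-efficacy, VCT attitude and VCT practice, expectation and response bias stays open as a rival explanation, together with confounding. The Step 4 percentages are conditional on the assumed shift and correlation and on a sizing test that is not the final analysis. The contradiction and the lack of credible masking do not depend on them.

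**What to change.** 1. Use one statement in the Abstract, Methods and Study design, and align the registry record with it: participants are not blinded to the treatment they receive. If it is true and consistent with the consent material, add that they are not told the hypothesis or which arm is under test.
2. Remove the double-blind wording and the claim that blinding protects against participant bias.
3. If blinding of researchers is intended, limit it to what can be done, such as an analyst working with arms coded A and B. This does not address participant expectation and should not be presented as if it did.
4. Reconcile the wait-list description in the Abstract with the e-book or leaflet comparator.
5. Report the self-reported primary outcomes, including VCT practice, as unblinded. State expectation and response bias as a limitation beside non-random allocation. Leave the ranking of the primary outcomes unchanged.
6. If a bias illustration is included, label the shift and the correlation as assumptions and show the range over both.

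The cost is wording in the article and the registry record, plus a coded arm variable if item 3 is adopted. The sample size, endpoints and model do not change. The design label becomes less favourable, and the bias itself is disclosed, not removed.
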